## Blinding

During this study, participants and statisticians will be blinded to the group assignments, but the acupuncturists will not be blinded. Before treatment begins, the acupuncturists will be informed of each participant’s identity and group assignment. The participants themselves, however, will be randomly divided into different groups (electroacupuncture and sham electroacupuncture) and will be blind to their assignments.

## Interventions

The acupuncturists providing treatment will be licenced and will have had at least 2 years of clinical experience.

All the acupuncturists who meet this standard will be trained before the trial begins on how to locate acupoints and non-acupoints, how to puncture and how to manipulate needles. Sterile disposable acupuncture needles (length 25–40 mm, diameter 0.25 mm; Hwatuo, Suzhou, China) and SDZ-V electroacupuncture instruments (Hwatuo, Suzhou, China) will be used. Acupuncture will be discontinued if a participant suffers from any adverse events (AEs). During the trial, participants will be prohibited from using treatments other than acupuncture.

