### Participant withdrawal criteria

Subject withdraws voluntarily;Subject experiences serious adverse reactions or serious complications, or a deterioration of the disease occurs in the course of the study, and it is not appropriate to allow continued participation.Subject displays poor compliance with the clinical trial protocols, an unwillingness to continue in the study, or requests to withdraw from the study;Subject is noncompliant with the prescribed treatment, or subject’s incomplete observation data affect the evaluation.

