### Participant discontinuation criteria

If there are serious adverse events, serious complications, or if subjects exhibit deterioration during the trial, the clinical trial will be suspended in accord with a doctor's judgement.

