### Participant elimination criteria

Participants that violate the inclusion and/or exclusion criteria.Participants in erroneous treatment groups.In the exit test, participants documenting the use of banned drugs or treatments and participants with incomplete data collection.

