## Sham electroacupuncture

Participants in the sham electroacupuncture group will receive treatment using blunt needles at the designated acupoints. Blunt needles have the appearance of real needles, but they do not penetrate the skin. The sham electroacupuncture group will receive treatment without needle manipulation for De qi, which is characterized by soreness, numbness, heaviness and a feeling of pressure. Non-acupoints are different from real acupoints or meridians and are shown in Table 3 and Fig. 3.

**Table 3 Tab3:** Locations of non-acupoints in sham-electroacupuncture group

Acupoints	Locations
Beside Feishu	1 cun^a^ beside Feishu (≈ 20 mm)
Beside Pishu	1 cun beside Pishu (≈ 20 mm)
Beside Shenshu	1 cun beside Shenshu (≈ 20 mm)
Beside Hegu	1 cun before Hegu (≈ 20 mm)
Beside Zusanli	1 cun backward Zusanli (≈ 20 mm)
Beside Sanyinjiao	1 cun backward Sanyinjiao (≈ 20 mm)
Beside Taichong	1 cun backward Taichong (≈ 20 mm)

^a^1 cun (≈ 20 mm) is defined as the width of the interphalangeal joint of volunteer’s thumb

The sham electroacupuncture procedure is as follows: the wire to the electroacupuncture instrument is cut off before the intervention. After the acupuncture procedure is completed, the non-acupoints are connected with electroacupuncture, and the parameters and course of treatment will be the same as those in the electroacupuncture group.

Considering ethical factors involved in this sham treatment, we will offer free acupuncture treatment and compensation to participants in the sham electroacupuncture group after all the conclusion of the trial.

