### Treatment of adverse events (AEs)

While focusing on efficacy, researchers must be alert to the occurrence of adverse reactions or AEs. When an AE is discovered, researchers will take necessary measures to treat the condition until the adverse event resolves. Adverse reactions or AEs, whether related to the study or not, will be recorded in detail, including date of onset, signs and symptoms, examination index, outcome, date of resolution, any actions taken, duration and follow-up. AEs should be resolved within 24 h. The common treatment-related AEs include fainting due to needle stick, subcutaneous haemorrhage, redness and swelling of the acupuncture site and continuous pain at acupuncture site.

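### Stopping acupuncture for any adverse event does not fit the serious-event threshold used elsewhere, and may stop treatment more often under electroacupuncture than under sham

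*Protocol article*

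**What the plan says.** On when treatment or participation ends, the protocol article has four statements:

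- **Interventions:** "Acupuncture will be discontinued if a participant suffers from any adverse events (AEs"). Nothing limits this by severity or relatedness, and nothing says whether the session or the remaining course is meant.
- **Participant withdrawal criteria:** "Subject experiences serious adverse reactions or serious complications, or a deterioration of the disease occurs in the course of the study", where going on is judged inappropriate.
- **Participant discontinuation criteria:** "If there are serious adverse events, serious complications, or if subjects exhibit deterioration during the trial, the clinical trial will be suspended", on a doctor's judgement. The heading concerns a participant; the sentence concerns the trial.
- **Treatment of adverse events (AEs):** events are treated until they resolve, with resolution expected within 24 hours. Stopping acupuncture is not mentioned. Events are recorded whether or not they are related to the study. The common treatment-related ones are fainting at needling and "subcutaneous haemorrhage, redness and swelling of the acupuncture site and continuous pain at acupuncture site".

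On the arms, electroacupuncture uses 14 insertions per session (Table 1, item 2a) with De qi required. For the sham needles the article says "they do not penetrate the skin", and the wire is cut. Acupuncturists know the assignment (Blinding).

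On data after a stop, withdrawn participants are to have a final assessment and be analysed (Treatment of withdrawn participants). Discontinued participants keep their data, with the last result taken as final (Treatment of participant discontinuation). Non-compliers are handled by randomisation and what appears to be multiple imputation (Clinical data analysis). Participant elimination criteria, however, remove "participants with incomplete data collection".

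**The concern.** A site that sees a minor needle-site reaction cannot tell from the article whether acupuncture ends, pauses or continues. Sites that follow different sections will stop different participants.

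The broad trigger is also unlikely to act equally on the two arms. Most of the listed treatment-related events need a needle through the skin, and the staff who apply the trigger know the assignment. If more electroacupuncture participants stop, that arm receives less of its planned treatment. If those who stop are then left unassessed or eliminated, the remaining participants are a selected group in one arm, and the comparison with sham is no longer fully protected by randomisation.

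**Working it through.** **1. One case, four sections.** Take a participant with a small subcutaneous haemorrhage that is not serious.

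- Interventions: acupuncture is discontinued.
- Participant withdrawal criteria: not met.
- Participant discontinuation criteria: not met.
- Treatment of adverse events: treat until resolved; silent on stopping.

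The article also does not say which data rule then applies: the one for withdrawn, discontinued, eliminated or non-complying participants.

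**2. The plan's own figure.** Sample size calculation: 24 per group with 20% attrition gives 24 / (1 − 0.20) = 30, and 5 × 30 = 150. This reproduces. The allowance is 30 − 24 = 6 participants per group.

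**3. Exposure.** Six sessions a week for 4 weeks is 24 sessions (Random allocation). Penetrating insertions per electroacupuncture participant: 14 × 24 = 336. Under sham: 0.

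**4. Treatment stops if any AE ends the course.** No AE rate is given, so the per-session risk p is an assumption. With independent sessions, P(at least one AE) = 1 − (1 − p)^24.

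| Assumed p per session | Participants stopped | Expected of 30 |
|---|---|---|
| 0.1% | 2.4% | 0.7 |
| 0.5% | 11.3% | 3.4 |
| 1% | 21.4% | 6.4 |
| 2% | 38.4% | 11.5 |
| 5% | 70.8% | 21.2 |

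The risk at which 20% of an arm would stop is p = 1 − 0.8^(1/24) = 0.93% per session.

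**5. How uneven the stops would be.** Let b be the risk over the course of an AE that can occur in either arm, and d the risk of a needle AE in the electroacupuncture arm only. Stop risk is 1 − (1 − b)(1 − d) under electroacupuncture and b under sham. Both b and d are assumptions.

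| d | b | Electroacupuncture | Sham | Share of stops under electroacupuncture |
|---|---|---|---|---|
| 20% | 0% | 20% | 0% | 100% |
| 20% | 5% | 24% | 5% | 0.24 / 0.29 = 83% |
| 20% | 10% | 28% | 10% | 0.28 / 0.38 = 74% |
| 20% | 20% | 36% | 20% | 0.36 / 0.56 = 64% |
| 5% | 20% | 24% | 20% | 0.24 / 0.44 = 55% |

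**6. From a stop to missing data.** A participant who stops needling can still have the week-4 scan and scales, and then nothing is lost. Data are lost if assessment also ends or if the elimination rule is applied. That rule conflicts with the three provisions that keep or impute data. Those provisions leave gaps of their own. Scans are planned only at baseline and after week 4, so without a week-4 scan the last result is the baseline scan and the recorded change is baseline − baseline = 0. The imputation sentence covers people who did not comply, whereas someone stopped under the Interventions rule has followed the protocol.

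**The case against.** The best defence is that the sections govern different things: stopping needling (Interventions), leaving the study (withdrawal criteria) and suspending the trial (the discontinuation sentence). A low threshold for stopping treatment can sit beside a higher one for leaving the study. This stands in part. A reader might infer that the other two sections allow acupuncture to stop only for serious events; neither says so. But the discontinuation criteria stand under a participant heading, and the section that follows them describes what happens to a discontinued participant, so the overlap is not removed.

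Second, discontinuation may mean only a pause. Treating an event until it resolves, within 24 hours, fits that reading, and the article does not settle it. All figures in the first table assume a permanent stop.

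Third, a reader might infer that nearly all stops would fall on electroacupuncture. That needs AEs under sham to be close to zero. The rule covers any AE, unrelated events count as AEs, and no rate is given for either arm.

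Fourth, a reader might infer that a 1% per-session risk uses up the 20% attrition allowance. The article does not support equating a treatment stop with a lost outcome, since three provisions keep or impute data. The independence assumption also matters: if AEs cluster in susceptible people, fewer participants are affected at the same average rate.

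Finally, a condensed article may leave grading and restart rules to the full protocol. That excuses missing detail, but not sections that disagree as printed.

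**Conclusion.** The inconsistency holds on the text. The trigger in Interventions is any AE, two sections use a serious-event or deterioration threshold, and a fourth treats AEs without mentioning a stop. An excess of treatment stops under electroacupuncture is plausible from the listed events, the non-penetrating sham and the unblinded acupuncturists.

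Its size is unknown. Across assumed risks of 0.1% to 5% per session, with permanent stops and independent sessions, about 2% to 71% of an arm would stop. In the scenarios with some AEs under sham, the electroacupuncture share of stops runs from 55% to 83%. Arm-dependent missing data are possible but not shown: they require that assessment ends or that elimination for incomplete data is applied. The point should be corrected; it is not a demonstrated bias.

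**What to change.** - Reconcile Interventions, Participant withdrawal criteria, Participant discontinuation criteria and Treatment of adverse events into one rule applied identically in both arms. State whether a stop means the session or the course, and whether the discontinuation sentence refers to the participant or the trial. What the rule should be is for the investigators.
- State that a participant who stops acupuncture for an AE stays in the randomised arm, has the week-4 scan and the scheduled assessments, and is not removed under Participant elimination criteria.
- Report AE-related stops by arm.

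The cost is protocol wording and continued follow-up of those who stop, at visits already scheduled. The sample size does not change.

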## Electroacupuncture

Participants allocated to the electroacupuncture group will receive treatment with needles inserted at previously designated points. Based on preliminary tests, the research group developed an acupoint matching scheme. The acupoints include bilateral Feishu (BL13), Pishu (BL20), Shenshu (BL23), Hegu (LI4), Zusanli (ST36), Sanyinjiao (SP6) and Taichong (LR3). All acupoints are localized according to the WHO Standard Acupuncture Locations and are shown in Table 2 and Fig. 3. All needles must achieve De qi (a sensation including soreness, numbness, distention, and heaviness), which is believed to be an essential component for acupuncture efficacy. After De qi, unilateral Feishu-Shenshu and Sanyinjiao-Taichong points will be used as the connection points of electroacupuncture. The density wave will be at a frequency of 2 Hz/100 Hz, and the current intensity will be in the range of 0.1~1.0 mA (according to the participant's comfort). A single session will last 30 min/day; 6 sessions will constitute a course of treatment, with 1 day of rest between courses; and the intervention will continue for 4 courses.

**Table 2 Tab2:** Locations of acupoints in electroacupuncture group

Acupoints	Locations^a^
Feishu (BL13)	On the back, under the spinous process of the 3rd thoracic vertebra, 1.5 cun laterally
Pishu (BL20)	On the back, under the spinous process of the 11th thoracic vertebra, 1.5 cun laterally
Shenshu (BL23)	On the back, under the spinous process of the 2nd lumbar vertebra, 1.5 cun beside the posterior midline
Hegu (LI4)	Between the 1st and 2nd metacarpal bones
Zusanli (ST36)	3 cun directly below Dubi, and one finger-breadth lateral to the anterior border of the tibia
Sanyinjiao (SP6)	Posterior to the mesial border of the tibia, and 3 cun above the tip of the medial malleolus
Taichong (LR3)	In the depression anterior to the junction of 1st and 2nd metatarsal bones

^a^1 cun (≈ 20 mm) is defined as the width of the interphalangeal joint of the volunteer’s thumb

**Fig. 3 Fig3:**
[figure not shown]
Locations of acupoints and non-acupoints

## Sham electroacupuncture

Participants in the sham electroacupuncture group will receive treatment using blunt needles at the designated acupoints. Blunt needles have the appearance of real needles, but they do not penetrate the skin. The sham electroacupuncture group will receive treatment without needle manipulation for De qi, which is characterized by soreness, numbness, heaviness and a feeling of pressure. Non-acupoints are different from real acupoints or meridians and are shown in Table 3 and Fig. 3.

**Table 3 Tab3:** Locations of non-acupoints in sham-electroacupuncture group

Acupoints	Locations
Beside Feishu	1 cun^a^ beside Feishu (≈ 20 mm)
Beside Pishu	1 cun beside Pishu (≈ 20 mm)
Beside Shenshu	1 cun beside Shenshu (≈ 20 mm)
Beside Hegu	1 cun before Hegu (≈ 20 mm)
Beside Zusanli	1 cun backward Zusanli (≈ 20 mm)
Beside Sanyinjiao	1 cun backward Sanyinjiao (≈ 20 mm)
Beside Taichong	1 cun backward Taichong (≈ 20 mm)

^a^1 cun (≈ 20 mm) is defined as the width of the interphalangeal joint of volunteer’s thumb

The sham electroacupuncture procedure is as follows: the wire to the electroacupuncture instrument is cut off before the intervention. After the acupuncture procedure is completed, the non-acupoints are connected with electroacupuncture, and the parameters and course of treatment will be the same as those in the electroacupuncture group.

Considering ethical factors involved in this sham treatment, we will offer free acupuncture treatment and compensation to participants in the sham electroacupuncture group after all the conclusion of the trial.

## Outcomes

### Primary outcomes

The primary goal of this study is to observe the degree of peripheral neuropathy and measure the subjective pain perceptions in participants with PDPN before and after acupuncture treatment and assess their correlation with the characteristics of the central sensitization state of the brain. We will measure the sensory nerve conduction velocity (SCV) and the current perception threshold (CPT) and will use the McGill Pain Scale while also combining multimodal brain imaging data for our correlation analysis.

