**Method and design:**

This will be a randomized controlled trial. A total of 150 participants will be recruited and assigned to one of three groups: the healthy group, the DM without PDPN group and the DM with PDPN group. Participants in the DM without PDPN and the DM with PDPN groups will each be further divided between an electroacupuncture group and a sham electroacupuncture group. Participants will receive six treatment sessions per week for 4 weeks. Multimodal cerebral imaging includes resting-state functional magnetic resonance imaging (rs-fMRI), diffusion tensor imaging (DTI) and magnetic resonance spectroscopy (MRS); this neurophysiological testing will be the primary outcome measure. Subjective pain scales and blood analysis will be a secondary outcome measure and will be used to assess the clinical efficacy of the intervention. Multimodal cerebral imaging will be used to detect cerebral activity changes in each treatment group. The clinical data and fMRI data will be analysed for all the groups. Multiple correlation regression analyses will be used to assess the association between changes in cerebral functional activity and the improvement of clinical outcomes after acupuncture treatment.

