#### Cerebral imaging index

The comprehensive application of multimodal cerebral imaging technology includes the use of rs-fMRI, MRS and DTI based on the BOLD effect. Based on the changes in the functional areas of the cerebral cortex, characteristics of functional connectivity in the whole cerebral cortex, functional connectivity between the cerebral cortex and subcortical nuclei and changes to the white matter and metabolic substances in the cerebral cortex, the objective is to analyse the functional and structural changes of cerebral central sensitization and its neuroimaging mechanism in participants with PDPN.

Based on the above results, participants with PDPN and non-PDPN will undergo multimodal cerebral imaging. The data for both groups will be compared and analysed for changes in cerebral functional areas, characteristics of whole cerebral functional connectivity, abnormal white matter and metabolic changes in the cerebral cortex. The aim of the analysis is to understand the mechanism of electroacupuncture in improving cerebral central sensitization in participants with PDPN.

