#### Neurophysiological index

The SCV of the bilateral superficial peroneal nerve will be measured by EMG. CPT will be performed at 2000 Hz, 250 Hz and 5 Hz, and for each group, the CPT values on the dorsal side of the first bilateral toe will be measured. The Short-Form McGill Pain Scale will be used to evaluate the subjective pain experienced by the subjects in each group. Multiple regression analysis will be performed to analyse the correlation between the SCV, CPT, McGill Pain Scale values and the multimodal cerebral imaging results to reveal and verify the relationship between the degree of peripheral neuropathy, subjective pain and the changes in cerebral function in participants with PDPN.

Based on the above results, the SCV of the bilateral superficial peroneal nerve, the CPT value of the dorsal side of the first toe and the Short-Form McGill Pain Scale will be recorded and evaluated in participants with PDPN after each electroacupuncture and sham electroacupuncture treatment. We will continue to use the method of multiple regression analysis to analyse the correlation between the SCV, CPT, McGill Pain Scale values and the results of the multimodal cerebral imaging to study the relationship between the clinical therapeutic effect of electroacupuncture and the improvement of cerebral central sensitization and reveal the mechanism of electroacupuncture in the treatment of PDPN.

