### Sample size calculation

This proposed study is an RCT whose primary aim is to evaluate the cerebral imaging mechanism of acupuncture to improve cerebral central sensitization and the clinical effect of acupuncture in patients with PDPN. Acupuncture is a complex intervention that differs from other treatments. Its therapeutic effect is changed if the acupoints are altered. No two-arm, randomized, sham-controlled trial has been conducted on this topic. For this reason, we are using our previous clinical experience to calculate the efficacy of electroacupuncture as an intervention [30, 31]. The proposed sample size of this trial was calculated mainly based on the Short-Form McGill Pain Questionnaire and the assumption that after treatment, the average change reported using this questionnaire would be greater for the experimental group than for the control group. The mean difference was 0.81, with a standard deviation of 0.07. Sample size was calculated using a noninferiority comparison. We set the alpha risk (*α*, type 1 error risk) at 0.025, the beta risk (*β*, type 2 error risk) at 0.2 and the critical value (*Δ*) at − 0.1. Calculating by using SAS [32], the sample size result was 24. Thus, according to this sample size calculation, each group should recruit 24 participants. Allowing for a 20% attrition rate in this study, we plan to recruit 150 participants, with 30 in each of the study groups. Healthy participants will not receive any treatment. Each participant will receive 2 rs-fMRI scans to observe different cerebral activities before and after acupuncture treatment.

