
### Clinical data analysis

According to the study data, the effect indices of the two groups will be calculated and compared to analyse the influence on the prognosis of PDPN. Indices of scales will be analysed by repeating measurement analysis of variance. The main analytical indicators will be the curative effect index and recurrence rate. A *t* test will be used for measurement data with a normal distribution. The Wilcoxon rank sum test will be used for nonnormal distribution; the Pearson chi-square test will be used for counting data. If it is a sequential concatenation table, the CMHX^2^ test will be used.

The measurement data of different treatment groups will be statistically described by the mean ± standard deviation (‾*χ* ± s). Intragroup differences will be assessed using a t-test at baseline; analysis of variance (ANOVA) will be used to compare measurement data at different stages; and SNK will be used for pairwise comparisons. Changes between groups before and after treatment will be analysed by ANOVA. If the data do not fit the above statistical analysis conditions (such as nonnormal), a nonparametric test will be used.

Counting data from different treatment groups are statistically described by frequency (constituent ratio). Changes between groups before and after treatment will be tested using the X2 test (CMHX2 test) or nonparametric test. The analysis of data results from participants not complying with the study protocol will be treated according to statistical analysis with randomization and multiple interpolation.

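### The primary outcome is given conflicting status across the protocol, and the two main clinical indicators in the analysis section are neither listed nor defined as outcomes

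*Protocol article*

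**What the plan says.** The protocol article speaks to what is primary in five places.

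- **Abstract, Method and design.** After naming rs-fMRI, DTI and MRS it says: "this neurophysiological testing will be the primary outcome measure. Subjective pain scales and blood analysis will be a secondary outcome measure".
- **Outcomes, Primary outcomes.** The stated goal is to observe neuropathy and pain in PDPN before and after treatment and to correlate them with cerebral sensitisation: "We will measure the sensory nerve conduction velocity (SCV) and the current perception threshold (CPT) and will use the McGill Pain Scale", combined with imaging. Two subsections follow, Cerebral imaging index and Neurophysiological index. The second covers SCV on both sides, CPT on both first toes ("CPT will be performed at 2000 Hz, 250 Hz and 5 Hz") and the Short-Form McGill.
- **Outcomes, Secondary outcomes.** The Short-Form McGill Pain Questionnaire has its own entry here, at baseline, weeks 1 to 4, and months 1, 2, 3 and 6.
- **Sample size calculation.** The primary aim covers both imaging mechanism and clinical effect. Then: "The proposed sample size of this trial was calculated mainly based on the Short-Form McGill Pain Questionnaire".
- **Clinical data analysis.** "The main analytical indicators will be the curative effect index and recurrence rate".

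On the contrast, Cerebral imaging index describes imaging in participants with and without PDPN and says: "The data for both groups will be compared and analysed for changes in cerebral functional areas". It gives the purpose as understanding how electroacupuncture acts on central sensitisation.

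**The concern.** A confirmatory trial needs one variable, at one time, in one comparison, on which its answer rests. Here the status of the pain scale changes from section to section, SCV and CPT are primary in the body but not clearly so in the Abstract, and the analysis section introduces two further main indicators that the outcome sections do not mention.

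The risk is selective reporting. A favourable result on imaging, SCV, CPT or the McGill, or on an index defined later, could be presented as the primary finding with a sentence of the protocol behind it. No separate analysis plan can follow all of these statements at once.

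The second issue is the comparison. The third objective (Background) is about the effect of electroacupuncture and needs the randomised electroacupuncture-versus-sham contrast. A before/after correlation and a comparison by disease status do not supply it.

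**Working it through.** **1. Status of each measure, section by section**

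| Measure | Abstract | Primary outcomes | Secondary outcomes | Sample size | Clinical data analysis |
|---|---|---|---|---|---|
| Imaging | primary | primary | – | part of the aim | – |
| SCV, CPT | not named | primary | – | – | – |
| Short-Form McGill | secondary (as a pain scale) | primary | secondary | sizing variable | – |
| Curative effect index, recurrence rate | – | – | – | – | main indicators |

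Imaging is consistent. The McGill is not. SCV and CPT are ambiguous: the Abstract attaches the word neurophysiological to imaging, while the body uses it for SCV, CPT and the McGill.

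**2. Timing of the McGill.** Neurophysiological index has it recorded after each electroacupuncture and sham treatment. The Secondary outcomes entry has it weekly during treatment and at four follow-ups. The first phrase may mean after every session or after each type of treatment. On neither reading does it match the second schedule, and no section names the time point that decides the trial.

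**3. The two main indicators.** The Outcomes sections contain no entry, formula, threshold or time point for either one. The BPI and McGill follow-ups to 6 months could feed a recurrence rate, but no recurrence event is defined.

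**4. The contrast.** Presence or absence of PDPN is fixed by the recruitment criteria, although Random allocation speaks of random assignment to the three populations. Only electroacupuncture versus sham, within each diabetic population (30 and 30), is truly randomised. A difference between PDPN and non-PDPN participants reflects the disease and whatever accompanies it, not the treatment.

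**5. The plan's own figure.** Inputs from Sample size calculation: difference 0.81, SD 0.07, margin 0.1, alpha 0.025 (taken as one-sided), power 80%. The normal-approximation formula is n per group = 2(1.960 + 0.842)² × SD² / (distance)².

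- Non-inferiority with true difference 0.81: 2 × 7.85 × 0.0049 / 0.91² = 0.09, so 1 per group (2 by noncentral t).
- Non-inferiority with true difference 0: 2 × 7.85 × 0.0049 / 0.1² = 7.7, so 8 (9 by noncentral t).
- Superiority with 0.81 read as a standardised difference (SD 1): 2 × 7.85 / 0.81² = 23.9, so 24 (25 by noncentral t). The document does not state this reading.
- Attrition: 24 / (1 − 0.2) = 30, and 5 × 30 = 150. This step reproduces.

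The stated 24 does not follow from the stated inputs. That is a separate defect, and the present point does not depend on it. It matters here only because the sizing must be rechecked whichever endpoint is chosen.

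**6. Illustration of the error risk.** With k independent tests at 0.05, the chance of at least one false positive is 1 − 0.95^k.

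- k = 4 (imaging, SCV, CPT, McGill): 1 − 0.95⁴ = 18.5%.
- k = 6 (CPT counted at three frequencies): 1 − 0.95⁶ = 26.5%.

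Correlation between measures lowers these figures, to 5% if they are fully correlated.

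**The case against.** The strongest reply is that the sections overlap more than they conflict. Imaging is primary in the Abstract and in the body. The sample size section declares no primary outcome; it sizes the trial on a clinical scale. The main indicators appear under the clinical analysis, apart from the neuroimaging analysis, so they can be read as main clinical indicators only. Formulas for derived indices are often left to an analysis plan. All of this stands, and it limits the point. It does not remove the contradictory status of the McGill, the uncertain place of SCV and CPT, or the use of the word main for measures that no outcome section lists.

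A reader might infer more than the document supports:

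- *That there are four mutually exclusive primary outcomes.* There are not, for the reasons just given.
- *That the sizing endpoint is formally secondary.* It is listed as both primary and secondary.
- *That the two indicators are measured nowhere.* The accurate statement is that they are neither listed nor defined; data already scheduled might supply them.
- *That the randomised contrast is absent.* The third objective specifies it, Neurophysiological index measures both arms in PDPN, and Clinical data analysis compares change between groups. What is missing is a single primary variable and time point attached to it.
- *That the false-positive risk is 46%.* This is 1 − 0.95¹², which needs 12 independent tests: 3 imaging modalities, 2 SCV sides, 6 CPT values and 1 McGill score. No section says that left and right are tested separately, and paired sides are plainly correlated.
- *That the McGill must be primary.* In a study of imaging mechanism that choice belongs to the sponsor.

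**Conclusion.** The point holds in this form: the current text contradicts itself on the status of the primary outcome, names two undefined main clinical indicators, and ties an aim about treatment mechanism to a comparison that is not randomised. These are conflicts between statements in the article, not detail that an article would leave to a fuller document.

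The consequence is a choice of primary result that stays open after the data are seen, with no stated error control across the candidates. Its size depends on how many measures are counted and how they correlate. The 18.5% for four measures assumes independence and a 0.05 threshold for each; the protocol states that threshold only for the correlation analysis. It is an illustration, not an estimate for this trial. The point should be settled before unblinding.

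**What to change.** 1. Name one primary variable, one time point and one contrast: electroacupuncture versus sham in the 60 randomised PDPN participants. Use it consistently in the Abstract, Primary outcomes, the secondary McGill entry, Sample size calculation and Clinical data analysis.
2. Choose the variable. Short-Form McGill change from baseline to week 4 matches the stated sizing variable and is already scheduled. If imaging is kept as primary, name a single imaging measure and base the sample size justification on it. In either case recheck the sizing; on the normal approximation, 24 completers per arm give 80% power at one-sided 0.025 for a standardised difference of 0.81.
3. Make the remaining measures secondary or exploratory, and give the McGill one schedule.
4. Assess the imaging mechanism by electroacupuncture versus sham change within PDPN. Label the PDPN, diabetes-only and healthy comparisons observational.
5. Remove the curative effect index and the recurrence rate as main indicators, or define them as secondary outcomes.

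The cost is a protocol amendment while recruitment is under way. It should be dated and should document that it was made before unblinding. Some measures lose primary status.
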